## End of the Study

The end of the study will be the last visit of the last participant.

Laboratory analyses will continue for 12 months.

## SELECTION AND WITHDRAWAL OF STUDY PARTICIPANTS

### Recruitment

The study will be done in the secondary care setting, across NHS sites in the UK (Including Scotland) where patients with cancer on CPIs are followed up and likely to present following a liver injury. Participants will be mainly recruited from oncology clinics and wards or from emergency departments when they present with acute symptoms. The initial approach will be from a member of the patient's usual care team (which may include the investigator or research team), and information about the study will be on display in the relevant clinical areas. Further visits will take place at the ward if patients remain hospitalised, at clinic following oncology follow up or at the Research Centres wherever is more convenient to the patients.

The investigator or their nominee, e.g. from the research team or a member of the participant's usual care team, will inform the participant or their nominated representative (other individual or other body with appropriate jurisdiction), of all aspects pertaining to participation in the study.

If needed, the usual hospital interpreter and translator services will be available to assist with discussion of the trial, the participant information sheets, and consent forms. The consent forms and information sheets will not be available printed in other languages.

It will be explained to the potential participant that that entry into the trial is entirely voluntary and that their treatment and care will not be affected by their decision. It will also be explained that they can withdraw at any time, but attempts will be made to avoid this occurrence. In the event of their withdrawal it will be explained that their data collected so far cannot be erased and we will seek consent to use the data in the final analyses where appropriate. Remaining tissue samples can be destroyed if the participant so wishes. We will explain to the participant that if they decide to withdraw after a long period of time, the samples may already have been used and we cannot recall samples or information from researchers if this is the case.

The Principal Investigator may also remove a subject if, in his / her opinion, it is in the best interests of the subject. If a patient permanently withdraws from the study, or is lost to follow-up, the reason will be recorded.

### Eligibility criteria

#### Inclusion criteria

Both patient groups and control group:

Aged 16 years and over

Able to give written informed consent OR

Potential participants who have developed encephalopathy related to ChILI as a response to checkpoint inhibitor therapy, who lack capacity to give written informed consent and have a consultee (personal or nominated) – for ChILI patient group only

#### ChILI Patients:

Adults with cancer receiving checkpoint inhibitors (CTLA-4, PD-1 or PD L1 inhibitor) as monotherapy or combination (without chemotherapy) and developed acute liver injury secondary to checkpoint inhibitor and meeting the following criteria will be included:

1. Meets one of the following analytical thresholds at enrolment (visit 1)
  - Alanine transaminase (ALT) exceeding 5 times upper limit of normal (ULN) OR
  - ALT exceeding 3 times ULN plus bilirubin exceeding 2 times ULN OR
  - Alkaline phosphatase (ALP) exceeding 2 times ULN with accompanying elevations of gamma-glutamyl transferase in the absence of known bone metastases driving the rise in ALP level
2. Absence of other known causes of liver injury after detailed investigations

Patients who developed ChILI but did not meet the above criteria at enrolment or who were found to have different cause for their liver injury after further investigations will be excluded from analysis

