### Part 3. Cross-sectional case/control study (comparing patients in parts 1 and 2)

We will run a cross-sectional case control study comparing biological samples of patients in the cohort study who did not develop ChILI after 6-14 weeks of CPI treatment (controls) with patients in the second study who developed ChILI (cases). A small percentage of patients in the cohort study (3-18%) will develop ChILI and will be added to the cases; they will have 4 visits in total (one prior CPI treatment and 3 visits following reaction). We will compare samples from visit 2 in controls (after 6-14 weeks of treatment without developing ChILI) and visit 1 in cases (time of reaction).

[figure not shown]

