#### Control Group:

Consecutive patients with cancer who have clinical indication to start checkpoint inhibitors will be approached for consent to be enrolled in the study. We will enrol 120 consecutive patients who will be identified as controls. A small proportion of patients will develop ChILI following their checkpoint inhibitor treatment and will be classified as cases.

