### **Exclusion criteria**

Anyone with any of the following conditions will not be included in the study:

- Patients who are treated with cytotoxic chemotherapy concurrently with checkpoint inhibitors.
- On the judgement of CI that the person has certain alternative explanation to the acute event (rather than ChILI).

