#### Sample size and justification

This is a mechanistic study to document the disease natural history rather than evaluate performance of specific biomarkers. As this uses specialist methods, we will only be able to recruit from a small number of suitable sites near to analytical facilities so sample size is limited by availability of suitable participants. Due to rarity of checkpoint inhibitors induced liver injury, incidence rate are between 3-18 % of patients receiving CPI, we aim to enrol 40 cases and 120 controls who received CPI without developing liver injury over 3 years. This is feasible at this centre based on current records of CPI treatment.

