### Secondary Outcome Measure

1. To identify risk factors and phenotypic features associated with ChILI and its association with other immune mediated adverse reactions.

2. To study the association between biomarkers, clinical features and development of ChILI.
3. To compare histological characteristics of ChILI with idiopathic auto-immune hepatitis and DILI due to other drugs.

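### The rule removing patients with another cause of liver injury acts on cases only, so in Part 3 such conditions are biased towards looking unrelated to ChILI or protective

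*Protocol*

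**What the plan says.** **Cases.** Under Eligibility criteria, ChILI Patients, a case must cross a biochemical threshold and also show "Absence of other known causes of liver injury after detailed investigations". The closing sentence of that section adds that those "who were found to have different cause for their liver injury after further investigations will be excluded from analysis".

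**Controls.** Under Control Group, "Consecutive patients with cancer who have clinical indication to start checkpoint inhibitors will be approached for consent to be enrolled in the study". No liver criterion is attached. Part 3 defines its controls only as Part 1 patients who are free of ChILI after 6-14 weeks of treatment.

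**Both groups.** The one related item under Exclusion criteria is "On the judgement of CI that the person has certain alternative explanation to the acute event (rather than ChILI". It is tied to an acute event, which a control does not have.

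**Overlap.** Part 3 also states: "A small percentage of patients in the cohort study (3-18%) will develop ChILI and will be added to the cases".

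**Use of the data.** Under Sample size and justification, "we aim to enrol 40 cases and 120 controls who received CPI without developing liver injury over 3 years". Secondary Outcome Measure, item 1, is "To identify risk factors and phenotypic features associated with ChILI and its association with other immune mediated adverse reactions". Statistical analysis compares clinical characteristics by chi-square or Wilcoxon/Kruskal-Wallis tests at P < 0.05. It does not say in which part this is done, and it sets no characteristics aside.

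**Work-up.** Appendix 1 lists the viral hepatitis screen, autoantibodies, ultrasound and alcohol assessment at Visit 1, in a table whose header covers controls and cases. No consequence for a control is attached to any result.

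**The concern.** The items that make up the liver work-up are natural candidate risk factors. They are also the evidence on which a suspected case may be reassigned to another cause and removed. A cohort patient with the same finding who never crosses the threshold stays in as a control. The exposure is thus thinned in one group by rule and left intact in the other.

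Two things are at stake. A condition that truly raises the risk of ChILI could appear neutral or protective in Part 3, and the study would then report the wrong lesson about patients with background liver disease. The biomarker comparison, which is a primary aim, uses the same two groups. If background liver disease also moves the candidate markers, its unequal presence could alter the contrast.

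**Working it through.** **Is there a figure to reproduce?** No. The 40 and 120 rest on feasibility, with no effect size, error rate or power. The check concerns the direction of the bias and how its size depends on two unknowns.

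**Inputs**
- 40 cases and 120 controls (protocol, Sample size and justification).
- p, the prevalence of a competing-cause condition among patients on checkpoint inhibitors. Not given; assumed 5% to 20%.
- f, the share of true would-be cases with the condition whom the rule removes. Not given; shown from 0 to 100%.
- Controls removed by the same rule: none (protocol, Part 3 and Control Group).

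**Formula.** Removing a share f of cases with the condition multiplies the odds of the condition among cases by (1 - f). The odds among controls, p/(1 - p), are untouched. Hence

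observed OR = true OR x (1 - f),

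whatever p is. With a true OR of 1, the prevalence left among cases is p(1 - f)/(1 - pf). Check at p = 10% and f = 50%: 0.05/0.95 = 0.053; case odds 0.0556; control odds 0.10/0.90 = 0.1111; ratio 0.50.

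**Observed odds ratio**

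| True OR | f = 0 | f = 25% | f = 50% | f = 75% | f = 100% |
|---|---|---|---|---|---|
| 1 | 1.00 | 0.75 | 0.50 | 0.25 | 0 |
| 2 | 2.00 | 1.50 | 1.00 | 0.50 | 0 |
| 3 | 3.00 | 2.25 | 1.50 | 0.75 | 0 |

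A true risk factor begins to look protective once f exceeds 1 - 1/(true OR): 50% for a true OR of 2, and 67% for a true OR of 3.

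**Would it reach P < 0.05 at 40 against 120, with a true OR of 1?**

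| p | f = 50%: chance of a significant result (normal approximation) | f = 100%: expected counts | Fisher p |
|---|---|---|---|
| 5% | about 6% | 0/40 v 6/120 | 0.34 |
| 10% | about 11% | 0/40 v 12/120 | 0.038 |
| 20% | about 22% | 0/40 v 24/120 | 0.001 |

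A significant false protective finding is therefore likely only when removal is close to complete and the condition is fairly common. Masking a real risk factor needs much less: partial removal is enough, and no test has to reach significance.

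**How many cases come from the cohort itself?** Of 120 cohort patients, 3% to 18% is 3.6 to 21.6. On that basis about 18 to 36 of the 40 cases come from Part 2.

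**The case against.** The strongest reply is that ChILI is a diagnosis of exclusion. A patient whose enzymes rose for another reason is not a case, and a control has no injury to attribute, so no parallel rule is owed. With perfect attribution no true case is lost, f is 0, and a true OR of 1 stays at 1. This stands as a limit on the size of the problem. It does not remove it, because a background condition is what makes it tempting to attribute a real ChILI episode elsewhere, and the protocol does nothing to measure how often that happens.

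Three stronger readings are tempting, and the documents do not support them.
- A reader might infer that liver disease as such bars a case. The wording concerns another cause of the injury. A patient with stable liver disease whose acute injury is attributed to the checkpoint inhibitor remains eligible.
- A reader might infer that cases and controls come from different populations. Both are cancer patients on checkpoint inhibitors without concurrent chemotherapy, and cohort patients who develop ChILI join the cases. The difference is selective removal from one group.
- A reader might infer that such conditions will look protective. Holding the cases at 2 of 40 against a prevalence of 10%, 20% or 30% in controls does give odds ratios of 0.47, 0.21 and 0.12 (Fisher p = 0.52, 0.026, 0.001). Since f = 1 - OR when the true OR is 1, those figures already assume that about 53%, 79% and 88% of such cases were removed.

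It can also be said that the synopsis links risk factors to the prospective cohort, that Study Configuration gives the case-control part the task of comparing biomarkers, and that adjustment may be left to an analysis plan not shown. That is fair. Even so, neither Statistical analysis nor Secondary Outcome Measure confines risk-factor work to Part 1. Who counts as a case or a control is fixed in the protocol.

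Finally, barring controls with liver findings from the main comparison would be a poor remedy. Cases with stable liver disease would remain, which reverses the asymmetry, and unusually healthy controls could inflate the AUC. This objection stands and shapes the fix.

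**Conclusion.** The point holds in a limited form. The competing-cause exclusion acts on cases only and nothing in the protocol offsets it. In Part 3, the association of ChILI with any condition that can serve as the competing cause is biased downward by the factor (1 - f) whenever some true ChILI is removed. It may then appear weakened, null or protective.

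The direction follows from the text. The size does not: f and p are assumptions throughout, and the bias vanishes if attribution is always correct. For the biomarker comparison the effect is uncertain. Controls with background liver disease are realistic comparators, so their presence calls for a sensitivity analysis and not for their exclusion. The point deserves a change of wording, because it bears on a stated secondary outcome and the remedy is cheap.

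**What to change.** 1. In Statistical analysis and Secondary Outcome Measure, state that conditions used to disqualify cases will not be tested or interpreted as ChILI risk factors in the Part 3 case-control data.
2. Examine those conditions only in the Part 1 cohort. The attribution rule operates there too, so add a sensitivity analysis that also counts threshold-meeting injuries attributed to another cause. Adjust the exclusion-from-analysis sentence under ChILI Patients so that these patients' data remain available for it.
3. Keep all controls in the main Part 3 biomarker comparison. Add a sensitivity comparison that leaves out controls, and any cases, with such a condition on the Appendix 1 Visit 1 work-up.

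**Cost.** The change is wording and a little more analysis, using work-up already scheduled. The restricted comparison is smaller: at an assumed prevalence of 5%, 10% or 20%, 120 controls fall to 114, 108 or 96, and some cases go as well. Risk-factor estimates for these conditions will be imprecise, because 120 cohort patients yield only about 4 to 22 ChILI cases at 3% to 18%. The main comparison and the recruitment targets do not change.

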## RATIONALE FOR CURRENT STUDY:

Despite remarkable progress in the treatment of several advanced malignancies with CPIs, immune mediated adverse events including checkpoint inhibitor-induced liver injury have been a real clinical challenge not only for physicians but also for cancer patients. This is due to the unpredictable nature of liver injury, lack of robust evidence to guide management and the potential consequences of stopping checkpoint inhibitor treatment. Current guidelines (European Society of Medical Oncology) suggest grading of the liver injury based on liver biochemistry test results: grade 1: alanine transaminase (ALT) or aspartate aminotransferase (AST) > 1 to 3 times upper limit of normal (ULN), grade 2 = ALT or AST >3 to 5 ULN, grade 3 = ALT or AST > 5 to 20 ULN and grade 4 = ALT or AST > 20 ULN [3]

Treatment guidelines for checkpoint inhibitor-induced liver injury are based on colitis and auto-immune hepatitis models with high dose corticosteroids being recommended for grade 3-4 liver injury or persistent grade 2 liver injury [3, 4]. However, steroids in cancer patients can cause serious adverse events and recent reports suggest that around 35% of grade 3/4 hepatitis regresses spontaneously without intervention [5, 6].

The immune-mediated liver injury induced by checkpoint inhibitors is much more frequent, a new and incompletely understood category of hepatotoxicity and distinct from other types of drug induced liver injury (DILI) such as direct or idiosyncratic DILI. Recent evidence suggests that ChILI is primarily mediated by CD8+ T cells, and it is associated with increased T cell activation and infiltration in the liver and with a characteristic histopathologic feature of necrotic/degenerative hepatocytes surrounded by ring-like T cell clusters [7]. This is different from direct chemically-induced, hepatocyte-intrinsic cell damage and death where hepatocyte cell death is typically the primary initiator of the inflammatory response [8]. This histologic feature is also different from autoimmune hepatitis or idiosyncratic DILI in humans [9].

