## STUDY TREATMENT AND REGIMEN

Suspected ChILI patients:

Biological samples will be collected from each enrolled patient on three occasions. These visits will take place as soon as possible following acute presentation; there will be a time lag of up to 2 weeks between identification of an episode of ChILI by the team responsible for the clinical care of the patients and the patient giving consent to take part in the study. Patients' blood tests must meet the eligibility criteria on the day they are enrolled (Day 0, visit 1) in order to participate in the ChILI study. Visit 2 will be 2-14 days from Visit 1. Visit 3 will be  $30 \pm 7$  days after the Visit 1.

As far as possible, research bloods will be collected at the same time as bloods for clinical care of the patient and visits arranged to coincide with hospital appointments. Preferred visit times are given below but visits outside the times will not be considered as a protocol deviation.

Appendix 1 lists the standard clinical care analyses (including ultrasound, viral hepatitis screen, autoantibody screen, haematology and blood chemistry), and research assessments which will be carried out at each visit.

For those who are in-patients (hospitalised at the time of acute ChILI) samples will be collected as part of clinical care and additional samples collected for research purposes.

At each visit a delegated member of the research team will collect:

- Up to 80ml of blood. See most recent study presentation and/or sample collection SOP for details.
- Up to **20 ml of urine if possible**
- A Stool sample will also be collected (if possible).

When considered appropriate by the clinical team, an additional optional 30ml blood will be requested at one or two visits. This will be collected in EDTA anti-coagulated tubes and

transferred directly to the research lab for processing immediately where this facility is available.

Patients may be consented and samples collected at their home if appropriate and with permission of the PI. Nursing staff would be required to follow their Trust's lone working policy and code of practice.

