#### Appendix 1. Patient assessment schedule

| Controls                                  | Before starting CPI         | After 6-14 weeks of treatment |           |
|-------------------------------------------|-----------------------------|-------------------------------|-----------|
| Cases                                     | Day 0
(date of reaction) | Day 7 (2-14 after Visit 1)    | Day 30 ±7 |
|                                           | Visit 1                     | Visit 2                       | Visit 3   |
| Inclusion/Exclusion criteria              | X                           |                               |           |
| Medical history/current medical condition | X                           |                               |           |

|                                                                                              |   |   |       |
|----------------------------------------------------------------------------------------------|---|---|-------|
| Demography                                                                                   | X |   |       |
| Body height                                                                                  | X |   |       |
| Body weight                                                                                  | X |   |       |
| Drug history in past 6 months, including OTC, herbal, dietary supplement, recreational drugs | X |   |       |
| Smoking history                                                                              | X |   |       |
| Alcohol, quantitative assessment                                                             | X |   |       |
| Viral hepatitis screen                                                                       | X |   |       |
| Autoantibody* screening                                                                      | X |   | (X)** |
| Liver ultrasound                                                                             | X |   |       |
| Standard clinical analysis: Hematology, Blood chemistry, (Urine analysis)                    | X | X | X     |
| Blood sample collection                                                                      | X | X | X     |
| Urine sample collection if possible                                                          | X | X | X     |
| Stool sample collection if possible                                                          | X | X | X     |

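### The enrolment-day threshold selects slower-resolving injury in Part 2, Visit 1 has two meanings, and the exclusion needs a stated scope so that it cannot reach the Part 1 incidence count

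*Protocol*

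**What the plan says.** Under Eligibility criteria, ChILI Patients, a case must meet one of three liver-test thresholds at Visit 1. The section closes with an exclusion covering two groups: those found to have another cause, and "Patients who developed ChILI but did not meet the above criteria at enrolment". Both "will be excluded from analysis". No study part and no particular analysis is named.

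Study Treatment and Regimen says that "there will be a time lag of up to 2 weeks between identification of an episode of ChILI" and the patient's consent. It adds that "blood tests must meet the eligibility criteria on the day they are enrolled", and labels that day Day 0, Visit 1. It also says that visits outside the preferred times are not protocol deviations.

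Other sections date the same visit differently. Appendix 1 heads the Day 0 column "date of reaction". Part 2 of Study Configuration and Participant Duration also place the first case visit at the reaction. Part 2 follows natural history for 1 month from enrolment.

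Incidence is calculated in the cohort group (Statistical analysis), which is Part 1. Those patients have their first visit before checkpoint inhibitor (CPI) treatment. If ChILI develops they become cases (Part 3; Control Group).

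**The concern.** A threshold applied after a delay is a filter on persistence. Two patients may have the same qualifying result on the day of identification. If one falls below the threshold before consent and the other does not, only the second enters Part 2. The study of what happens after ChILI (first secondary objective) would then describe the more persistent part of the disease without saying so.

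The protocol gives a reason to expect such patients. Its Rationale cites reports that "around 35% of grade 3/4 hepatitis regresses spontaneously without intervention". By the grading quoted there, grade 3 begins just above 5 times the upper limit of normal (ULN), which is also the ALT entry threshold.

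A second problem is time zero. If Visit 1 can fall 14 days after identification, it cannot also be the reaction date for every case. Patients with different lags would be lined up as though at the same stage of injury.

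A third is scope. Part 1 patients who develop ChILI are also called cases, and the exclusion is not confined to Part 2. A primary outcome therefore depends on how an unqualified sentence is read.

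**Working it through.** The protocol gives no power or precision calculation, so there is no stated figure to reproduce.

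**1. The clock (protocol figures only, taking consent and Visit 1 as the same day).** The lag from identification to Visit 1 is 0 to 14 days. Visit 2 is 2 to 14 days after Visit 1, and Visit 3 is 30 ± 7 days after it.

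| | If Visit 1 is the reaction date | With the permitted lag |
|---|---|---|
| Visit 1 | day 0 | day 0 to 14 |
| Visit 2 | day 2 to 14 | 0+2 to 14+14 = day 2 to 28 |
| Visit 3 | day 23 to 37 | 0+23 to 14+37 = day 23 to 51 |

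The right-hand column counts from identification. If the first qualifying test came earlier than identification, the spread is wider.

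**2. How many cases are exposed.** The target is 40 cases and 120 ChILI-free controls, with incidence of 3 to 18% (Sample size and justification). Part 1 then needs 120/(1−p) patients:

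- p = 3%: 120/0.97 = 123.7, with 3.7 cases; 40 − 3.7 = 36.3 must come from Part 2.
- p = 18%: 120/0.82 = 146.3, with 26.3 cases; 40 − 26.3 = 13.7 must come from Part 2.

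So about 14 to 36 of the 40 cases enter by the route with the lag. If 120 is instead the whole of Part 1, the figures are 40 − 21.6 = 18.4 to 40 − 3.6 = 36.4.

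**3. Direction and possible size of the selection (assumptions).** The documents give no peak ALT and no rate of fall. Assume ALT halves every T days from identification. The time to fall to 5 × ULN is T × log2(peak/5).

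- T = 7, peak 8 × ULN: 7 × log2(1.6) = 4.7 days.
- T = 7, peak 10 × ULN: 7 × log2(2) = 7.0 days.
- Peak 8 × ULN with T from 3 to 14 days: 2.0 to 9.5 days.

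All fall inside the 14-day lag. A simulation took the lag as uniform on 0 to 14 days, peak ALT as 5 plus a lognormal (median peak 10 × ULN) and T as lognormal. It used the ALT > 5 × ULN criterion only.

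| Median T, all cases (days) | Still eligible at Visit 1 | Median T, those kept (days) |
|---|---|---|
| 5 | 42% | 6.2 |
| 7 | 54% | 8.4 |
| 10 | 68% | 11.4 |
| 14 | 79% | 15.4 |

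Median peak ALT among those kept rises from 10 to between 11.0 and 12.2 × ULN. The direction is the same in every row. The size depends on the assumptions, and patients who still qualify by another threshold would reduce it.

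**4. Part 1 incidence.** The lag ends at consent, and Part 1 patients consent before CPI, so it does not apply to them. Patients lost from Part 2 enter neither the numerator nor the denominator of the incidence. That leaves the exclusion sentence:

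- Read literally, enrolment for a Part 1 patient is the pre-treatment visit. No ChILI threshold would be expected to be met then, so every Part 1 case would be excluded. That cannot be intended.
- Read as applying at the reaction visit, it would drop a Part 1 patient whose episode had settled by then. Control Visit 2 is only for patients without ChILI, so that patient would have no assigned place.
- Read as applying to Part 2 only, incidence is untouched.

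The text does not choose between these readings, so no loss can be derived. For scale under the second reading, suppose a share m of episodes is lost from both numerator and denominator; incidence becomes p(1−m)/(1−pm). With m assumed at 10 to 50%, a true 18% becomes 16.5 to 9.9%, and a true 3% becomes 2.7 to 1.5%.

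**The case against.** The best reply is that the rule suits its purpose. This is a descriptive, mechanistic study. Requiring active injury when the sample is drawn is right for the biomarker comparison, and Part 2 says openly that its month runs from enrolment. Natural history is a secondary objective and no time-to-recovery endpoint is named. The exclusion also covers patients who never met a threshold, and leaving them out is a consistent case definition. All of this stands. It supports keeping the threshold for Part 3. It does not reconcile the two meanings of Visit 1, and it does not tell a reader which patients the natural history describes.

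Three stronger readings are tempting and are not supported:

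- A reader might infer that the 2-week lag lowers the primary incidence. Part 1 patients consent before treatment, so it does not.
- A reader might take the 35% regression figure as the share of cases lost. It concerns grade 3/4 hepatitis without intervention, and the protocol gives no timing, so it cannot be turned into a loss within 14 days.
- A reader might say that the protocol treats spontaneous regression as a central question. It only cites reports of it, in contrast with the harms of steroids.

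**Conclusion.** The point holds for Part 2 and for the definition of Visit 1. Followed as written, the entry rule selects slower-resolving injury and puts time zero up to 14 days after identification, so that Visit 3 spans days 23 to 51. About 14 to 36 of the 40 planned cases come by this route, given the protocol's 3 to 18% incidence and a full set of 120 ChILI-free controls. The direction of the selection is secure. Its size is not, because the 42 to 79% still eligible rests on assumed ALT kinetics and an assumed uniform lag.

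For Part 1 incidence the defect is one of scope. The consent lag causes no bias there, but the exclusion sentence, taken at its word, would remove Part 1 cases. How many events would be lost in practice cannot be derived from the documents.

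**What to change.** 1. **ChILI Patients (Eligibility criteria).** State that the enrolment-day exclusion does not apply to the Part 1 incidence count. Count every cohort patient with any liver test meeting the thresholds during the follow-up window after CPI start, other causes excluded, whatever the value on the reaction-visit day. It must be any test, because counting only the first test after treatment starts would miss later onset.
2. **Part 2, Participant Duration, Study Treatment and Regimen, Appendix 1.** Use one definition: the reaction date is the date of the first test that meets the thresholds. Record that date and value and the lag to Visit 1, and describe natural history from that date. If time to recovery is analysed, treat Visit 1 as delayed entry, since nobody in Part 2 can have recovered before it.
3. **Part 3 and Part 2 reporting.** Keep the Visit 1 threshold for the at-reaction biomarker comparison. State that Part 2 natural-history results apply to patients still above threshold at enrolment. Narrowing the exclusion sentence alone would not remove the selection, because the entry rule in Study Treatment and Regimen would still apply.

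The cost is a wording change and one date and value per case from routine results; the case report form is not among the documents and may already hold them. The natural-history conclusion is then stated for a narrower population.
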